**Figure 1 figure1:**
[figure not shown]
Visual outline of the experimental design. In phase 2 of the virtual reality experience, participants engage in the embodiment task.

Additionally, a separate pilot study will be conducted with 10 couples, allowing for the evaluation of the performance of the application prior to full-scale implementation.

Participant recruitment will occur between May 2026 and May 2027.

### Patient and Public Involvement

Female survivors of sexual harassment and professionals working with male offenders will be involved in the cocreation of the VR scenarios used in the REVISE intervention. Their contributions will ensure that the immersive scenes are emotionally realistic, ethically appropriate, and contextually relevant for the target population. Their involvement will help refine the language, content, and narrative flow of the scenes.

### Primary Outcome

The AMMSA scale [32] will be used to assess changes in beliefs about sexual aggression (justification or minimization, subtle beliefs). This study will use a Spanish-adapted and validated version [33]. The scale consists of 30 items rated on a 7-point Likert scale ranging from 1 (“totally disagree”) to 7 (“totally agree”). Higher scores indicate greater acceptance of modern myths about sexual aggression. In a Spanish sample, the scale demonstrated high internal consistency (Cronbach α=0.91). An example item is “Alcohol is often the culprit when a man rapes a woman.”

### Secondary Outcomes

#### Changes in Empathy

We will use the Spanish-validated version of the Interpersonal Reactivity Index [34,35]. This scale evaluates the cognitive and emotional reactions of an individual to the observed experiences of another person, that is, empathy. It consists of 28 items answered on a 5-point Likert scale. We will use the Spanish-validated version [35]. The Interpersonal Reactivity Index assesses 4 different dimensions related to empathy, namely perspective taking, fantasy, empathic concern, and personal distress. Cronbach α of this index ranged from 0.68 to 0.80. An example item is “I would describe myself as a fairly soft-hearted person.”

#### Changes in Gender Role Attitudes

We will use the brief version of the Ambivalent Sexism Inventory [36], which is composed of 12 items, scaled with a 6-point Likert scale (0=strongly disagree to 5=strongly agree). It assesses sexist attitudes. We will use the Spanish brief validated scale [37], 6 items from the Hostile Sexism subscale and 6 items from the Benevolent Sexism subscale. Higher scores indicate a greater presence of sexism against women. Cronbach alphas of the scale were 0.75 and 0.81, respectively [37]. One item as an example is “Men are more willing to put themselves in danger to protect others.”

#### Changes in Couple Communication Patterns

We will use the Communication Patterns Questionnaire (CPQ) [38]. The Spanish version of the CPQ [39] will be used in this study. It is a self-report that measures the communication patterns in close relationships. It assesses 3 dimensions of communication: mutual constructive communication, communication avoidance or demand/withdrawal, and aggressive communication. The questionnaire is answered with a scale of possible use of the strategy, with 9 response options, from “very unlikely” to “very likely,” and in its current form, it is composed of 24 items. One example is “Both my partner and I blame, accuse, and criticize one another.” The Cronbach α in Spain ranged from 0.62 to 0.84.

#### Changes in Relationship Satisfaction

We will use the brief Spanish version of the Dyadic Adjustment Scale [40,41], which consists of 13 items rated on a Likert scale with variable response formats. The scale measures couple adjustment by grouping items under 3 second-order factors and a first-order structure. Scores ranged from 0 to 63, with 44 as the cutoff point to distinguish between high and low couple adjustment. Higher scores indicate better couple adjustment. For example, one item asks, “How often have you thought about divorce or separation?” with response options ranging from “never” (0) to “all the time” (5). Another item, “Do you and your partner calmly discuss any topic?” is rated from “never” (0) to “very often” (5). The scale has demonstrated good internal consistency, with a Cronbach α of 0.83.

#### Changes in Couple Flourishing

We will use the Couple Flourishing Measure [42], the Spanish version of Saavedra-Roa et al [43,44] will be used. It is a unidimensional instrument consisting of 16 items designed to be completed individually, which assesses couple flourishing using a 7-point visual analogue Likert scale. The scale ranges from 1=distressed relationship, 4=satisfied relationship, and 7=flourishing relationship. An example of an item is “Quality time spent alone with my partner is...,” where 1=monotonous (distressed), 4=pleasant (satisfied), and 7=memorable (flourishing). Scores range from 16 to 112, with higher scores indicating greater couple flourishing. The instrument demonstrated high internal consistency reliability (α=.94).

#### Change in Body Ownership Illusion

To assess body ownership and agency from a first-person perspective, a validated 4-item scale will be administered verbally at two time points during the IVR experience (see Figure 1 and Table 1):

Mirror embodiment phase: The assistant will ask participants to look at a virtual mirror and rate, on a scale from 0 to 10, the extent to which they felt that the virtual body reflected in the mirror was their own. Participants will then look down and respond to the same question regarding their virtual bodies.Farewell phase: At the end of the IVR session, participants will answer two additional questions: “Did you feel that you owned a different body during the experiment?” and “Did you feel fear of aggression at any point in the experiment?” on the same scale (0-10).

**Table 1 table1:** Trial schedule.

Time point	Preintervention	Allocation	Postallocation		
		0	Intervention day	1 week after intervention^a^	3 months follow-up^b^
Enrollment	✓				
Eligibility screen	✓				
Informed consent	✓				
Allocation randomization		✓			
Baseline			✓		
Embodyment task			✓		
IVR^c^ exposure condition 1			✓		
IVR exposure condition 2			✓		
IVR exposure condition 3			✓		
Self-report assessment^d^			✓	✓	✓
Physiological measures (eye-tracking and pupillometry)			✓		
Change interview			✓	✓	✓

^a^The 1-week postintervention evaluation examines short-term retention of intervention effects.

^b^The 3-month follow-up was chosen to assess long-term changes.

^c^IVR: immersive virtual reality.

^d^Self-report assessments include Interpersonal Reactivity Index (IRI), Ambivalent Sexism Inventory (ASI), Communication Patterns Questionnaire (CPQ), Acceptance of Modern Myths About Sexual Aggression (AMMSA) Scale, Dyadic Adjustment Scale (DAS), Couple Flourishing Measure (CFM), Self-Assessment Manikin (SAM), and body ownership.

#### Changes in Affective Responses

Self-Assessment Manikin (SAM) will be used [45]. This is a pictorial scale where a manikin is shown to indicate the affective reaction of a person to a given stimulus. The SAM is answered on a 9-point visual analogue scale. Valence (SAM-V), also known as pleasure, arousal (SAM-A), and dominance (SAM-D), will be used for this experiment.

#### Eye Tracking

Eye tracking is an experimental method for recording eye motion and gaze location over time and across different conditions. This is a common method of observing the allocation of visual attention [46]. In this project, it will be used to measure attention to erotic stimuli. According to sexual objectification theory, this is related to sexual aggression [47,48]. VR goggles compatible with an eye-tracking system will be used. Two different parameters will be collected: (1) number of fixations, that is, number of available fixations on the specified area of interest, which is the VR model neckline, and (2) dwell time or complete fixation time, that is, the sum of the fixation duration at the specified area (neckline) in milliseconds. In this study, the exact duration used to define a single fixation will be 100 milliseconds.

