### Intervention Procedure

The intervention follows 5 phases, as shown in Figure 1. Each participant will arrive at the laboratory and provide their consent to participate in the study. They will be randomly assigned; participants will be naïve to the study hypotheses. While avatar creation takes place, the couple will answer preintervention questionnaires. Phase 1 also involves the process of personification of the avatar according to the condition in which they will be assigned (see the section on the Intervention Description).

During phase 2, the participants will perform a mirror embodiment task to familiarize themselves with the virtual environment and their new virtual body. More specifically, a female virtual assistant will welcome the participants and instruct them to perform some physical body movements while observing themselves in a virtual mirror. The observation of real-time movements in the embodied avatar, which corresponds to the participants’ real body movements, will allow for greater immersion, as well as enhance body ownership and agency toward the virtual body. For assessment purposes, the female assistant will be a sexualized avatar. During this initial outreach, eye-tracking data will be collected from the participants in relation to the assistant’s cleavage, as gaze fixation on sexualized body parts has been identified as a marker of sexual objectification [47,52]. Once the training and embodiment process is completed, participants will be asked the first questions related to embodiment to check the degree of embodiment achieved.

In phase 3, men will have a 180-second adaptation period in which they will be in an empty bar, and nothing will happen, while women will be in a neutral playful setting in all 3 conditions. Condition 1 men will be involved in a situation of sexual harassment by a group of other men (eg, unwanted flirting, verbal intimidation, and sexist comments). In condition 2, they will stay the same length of time as in the other conditions, but in this case, they will not be sexually harassed. Finally, those in condition 3 will witness the same harassment as in condition 1, but from a bystander perspective, that is, the assaulted person will be a random virtual woman. While people are exposed to the scenarios, their emotional arousal will be assessed by pupillometry in the 3 experimental conditions; however, SAM will be used at the end of phase 3.

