Phase 4 will be similar for the 3 conditions. In condition 1, men will have a virtual meeting with their partners (both still with the exchanged identity) outside the context in which the harassment situation occurred. The man will be asked to recount his experience related to the harassment experienced virtually to his partner, who will then be asked to respond empathetically. In condition 2, participants will also meet with their partners (maintaining the virtual identity exchange) outside the scenario in which they were and will be asked to discuss their concerns and expectations of the relationship related to gender issues. In condition 3, participants will discuss the sexual harassment they witnessed in the bar scene, while embodying their own avatar (not exchanged). This discussion will emphasize their reflections on the observed behavior and its consequences, promoting personal insights from their perspective as bystanders.

In phase 5, the sexualized female avatar will appear to perform the farewell, and the participants’ gaze will be traced. Before the end, two questions related to body belonging will be asked. Outcome assessments will be conducted immediately after the intervention (posttest) and at 3 months (follow-up).

The intervention will be discontinued for a participant if they experience severe cybersickness (eg, nausea, dizziness, and disorientation), acute psychological distress, or technical failures that compromise the integrity of the experience or data collection. Participants will be informed that they may request to stop the session at any time without providing a reason. In such cases, the session will be immediately terminated, and appropriate support will be offered if needed.

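### Gaze is scored only in absolute terms on the neckline, so a difference against condition 3, or a phase 2 to phase 5 change, is not specific to sexual objectification

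*Protocol article*

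**What the plan says.** The Eye Tracking section states the purpose: "In this project, it will be used to measure attention to erotic stimuli". It then gives a closed list, "Two different parameters will be collected": first, "number of available fixations on the specified area of interest, which is the VR model neckline"; second, dwell time, defined as "the sum of the fixation duration at the specified area (neckline) in milliseconds". Both are absolute quantities on one area.

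Intervention Procedure describes two recordings. In phase 2 a sexualised assistant welcomes the participants and will "instruct them to perform some physical body movements while observing themselves in a virtual mirror"; during this stage "eye-tracking data will be collected from the participants in relation to the assistant’s cleavage". The reason given is that "gaze fixation on sexualized body parts has been identified as a marker of sexual objectification". In phase 5, "the sexualized female avatar will appear to perform the farewell, and the participants’ gaze will be traced".

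The second of the secondary objectives compares eye-tracking responses across conditions. The Secondary Outcomes paragraph of the Data Analysis Plan gives secondary outcomes the primary model's condition, time and interaction terms, and assigns the eye-tracking measures to linear mixed models with random intercepts. The article names no reference area such as the assistant's face or body, no proportion of gaze and no total-gaze covariate.

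**The concern.** Neckline dwell has two components: how long a man looks at the assistant at all, and what fraction of that time falls on the neckline. The second shows selective attention to the sexualised part. The first can move for reasons unrelated to objectification.

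Phase 2 supplies such a reason. The mirror competes with the assistant for gaze, and what it shows depends on the arm: the partner's body in conditions 1 and 2, the man's own avatar in condition 3. If men in a partner's body look longer at the reflection and less at the assistant, raw neckline dwell and fixation count both fall in conditions 1 and 2 without any change in selectivity. That could be reported as less objectifying gaze. The error can also run the other way, with a real fall in selectivity masked by more looking overall.

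**Working it through.** The article gives no gaze data, expected gaze effect or gaze power, so there is no figure to reproduce. The check is on the definition, followed by an illustration.

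**1. Decomposition.** Neckline dwell = total dwell on the assistant × neckline share.
- 30 s × 10% = 3,000 ms
- 15 s × 20% = 3,000 ms

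The scores are equal, but the second man is twice as selective.

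**2. Which comparisons are exposed.**
- Condition 1 or 2 against condition 3 in phase 2: exposed, because the mirror content differs.
- Condition 1 against condition 2: not exposed to this mechanism, because both embody the partner.
- Phase 2 to phase 5: no mirror is described for phase 5. A shift in looking that is stable over both phases cancels in the condition × time term. A shift confined to phase 2 does not cancel and appears as an interaction.
- Phase 2 as a baseline: the avatar is prepared according to the allocated condition in phase 1, so phase 2 gaze is recorded after allocation in the allocated body. Participant random intercepts absorb stable individual differences, not shifts specific to an arm.

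**3. Illustration A.** From the article (Sample): 30 couples, hence 30 men, per arm. Assumed: a 120 s phase; mean neckline share 12% in both arms (Beta, precision 15); time on the assistant 60% in one arm and m in the other (Beta, precision 12); two-sample t test at 0.05; 5,000 trials per setting. Mean raw dwell = 120 × m × 0.12.

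| m in other arm | Mean raw dwell | Raw test rejects |
|---|---|---|
| 60% | 8.6 s | 5.3% |
| 50% | 7.2 s | 15.1% |
| 40% | 5.8 s | 51.1% |
| 30% | 4.3 s | 91.6% |

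The test on the share rejects in 4.8% to 5.4% throughout.

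**4. Illustration B, under different assumptions.** 30 men per arm; mean 30 s on the assistant with coefficient of variation 0.4; share 10% with Beta concentration 20 or 100; t test on log neckline ms or on the share; 4,000 runs. Rejection rates are shown as concentration 20 / concentration 100.

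| Second arm relative to first | Raw dwell (log ms) | Share |
|---|---|---|
| Same looking, same share | 5% / 6% | 5% / 5% |
| Looking −25%, same share | 25% / 61% | 5% / 6% |
| Looking −40%, same share | 62% / 98% | 5% / 5% |
| Looking −50%, same share | 86% / 100% | 5% / 5% |
| Same looking, share −40% | 77% / 98% | 74% / 100% |
| Share −40%, offset by more looking | 10% / 5% | 74% / 100% |

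In the last row the share falls from 10% to 6% while looking rises from 30 s to 30/0.6 = 50 s, and 50 s × 6% = 3 s, the same as 30 s × 10%. The fifth row shows that raw dwell performs well when overall looking does not differ between arms.

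**The case against.** A reader might infer that the score merely records how much men look at the assistant, or that it cannot be compared between arms. The documents support neither reading. A man who watches only the assistant's face scores zero. Couples are randomised, and no difference in the assistant between arms is described, so neckline gaze can be compared validly as neckline gaze. It also matches the purpose stated in the Eye Tracking section.

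The article does not define objectification as a share. It rests the link between gaze and objectification on cited sources that are not available here. A general fall in looking at a sexualised figure could itself be an intervention effect, and a share would discard it. This stands, and it is why raw dwell should keep its place.

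The mechanism is also limited: it does not touch condition 1 against condition 2, and it is described only for phase 2. The instruction to look down at the body, in Change in Body Ownership Illusion, belongs to the embodiment ratings, which appear to follow the phase 2 gaze recording, so nothing is built on it here. The assumed gaps in looking have no source in the documents.

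Finally, an article may leave normalisation to a fuller document. That carries less weight here, because the article itself fixes two parameters and one area, and then attaches the interpretation to them.

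**Conclusion.** The point holds as a limit on interpretation. Raw neckline count and dwell are valid measures of attention to the neckline, but they mix overall looking with selectivity. A raw difference involving condition 3, or a change from phase 2 to phase 5, is therefore not specific to the objectification reading in Intervention Procedure. Randomisation makes a raw difference causal but does not show which component moved.

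The size is unknown. The rejection rates are illustrations that depend on assumed gaps in looking; with no gap, raw dwell is sound. The outcome is secondary, and the primary belief outcome is unaffected. The change is still worth making, because it decides what the gaze result can support.

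**What to change.** In Eye Tracking, define areas of interest for the assistant's face and remaining body as well as the neckline, from the same recording in phases 2 and 5. Prespecify three quantities side by side:

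- raw neckline dwell and fixation count, as now;
- total time on the assistant;
- neckline dwell as a share of total dwell on the assistant; for counts, neckline fixations in a Poisson or negative binomial model with an offset of log(total fixations on the assistant). The Data Analysis Plan already names these models for count outcomes.

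State that an arm difference will be interpreted as specific to objectification only if it appears in the share, and otherwise as a difference in attention to the neckline. State also that phase 2 gaze is recorded after allocation and is not a pre-randomisation baseline.

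The cost is two more areas tagged on one avatar, plus wording; there is no new procedure or participant burden. The article reports that recruitment had not begun as of January 2026, and the planned 10-couple pilot could test the tagging. If only neckline fixations were stored, the denominator might not be recoverable later. The downside is small: the share is noisy for men who rarely look at the assistant and undefined for a man who never does, so weight it by total assistant dwell or rely on the offset model, and say how zero totals are handled.

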#### Pupillometry

It is the measurement of minute fluctuations in pupil diameter in response to a stimulus. Pupil dilation is thought to index autonomic activity; thus, negative stimuli trigger larger pupil dilation [49,50]. Pupillometry has recently been used to effectively evaluate the emotional effect of a nonconsented sex film clip visualization (woman as recipient) in men [50]. We will compute the pupil diameter ratio. Pupil data will be sampled at least 60 Hz, with a visual angle accuracy of 0.5. Pupil amplitude artifacts (<1 mm or >9 mm) as well as drifts and blinks will be coded as missing values [51]. As suggested, pupil data will be smoothed using a 10 Hz low-pass filter as suggested by Carvalho et al [52].

#### Change Interview

This semistructured script interview was created to assess the changes produced throughout the therapy, the useful aspects, and the adverse effects of interventions from the client’s perspective [53]. Clients are asked about the changes they have experienced with the intervention, as well as the negative changes, if any. Questions are also asked regarding the attribution of such changes and their probability of occurrence without intervention. Its functions in this study are to identify both changes that clients are aware of (in their own words), which might go unnoticed with standardized questionnaires, and adverse effects (too often neglected in research).

### Experimental Design

#### Overview

This study will seek to evaluate the efficacy of REVISE for reducing beliefs related to sexual aggression and influencing related psychological mechanisms, such as empathy and perspective-taking, among heterosexual men. The study includes 3 IVR intervention scenarios (see Figure 1). All conditions will follow the same general format: a 1-hour main session, where participants will be exposed to an IVR setting, followed by a postintervention interview to assess the impact of the experience and follow-up (for details, see Figure 1 and Table 1).

Self-reported questionnaires assessing empathy, gender attitudes, attitudes about sexual aggression, and relationship dynamics will be administered at 3 time points: baseline (preintervention), immediately postintervention, and at a 3-month follow-up. Physiological measures, including eye tracking and pupillometry, will be recorded in real time during IVR exposure to capture participants’ attention and emotional responses. Additionally, questions assessing embodiment will be administered at two key moments during the IVR session: (1) after the mirror embodiment phase and (2) at the end of the experience (farewell phase). Finally, a semistructured interview will be conducted immediately postintervention to explore participants’ subjective experiences, perceptions of the IVR scenario, and reflections on the impact of the intervention on their attitudes and beliefs related to sexual harassment and gender-based violence. The 3 experimental conditions are described in the following subsections.

